### Allocation

Most families will be allocated on an individual basis using computer-generated randomizing, giving them an equal chance of being allocated to the intervention or the control group. If more families are recruited than the number of available volunteers, randomization will be proportional using computer-generated randomizing (eg, if there are five available volunteers and seven recruited families, five of the seven families will be randomly allocated to the intervention group and two to the usual care group).

Family group random allocation will be the responsibility of the research program manager who will be blind to any details about the family when making this allocation. Once the allocation is determined, the program manager will notify the appropriate program coordinator. It will not be possible to blind the research staff responsible for data collection: families will know their allocation and are likely to disclose this to the researchers during data collection. While data collection is not blind, data analysis will be blind, completed by team members who have not been involved in data collection.

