### Participants

#### Eligibility Criteria

Eligible families will be those who meet the following criteria: (1) families having one or more children in the 0-5 age range; (2) families at risk of geographic or social isolation (eg, separated from usual support networks due to immigration); (3) parents seeking to develop confidence and increase their parenting knowledge and skills; (4) families residing in the specified service area; and (5) families unable to resource or access other support services (eg, due to financial hardship). Language translation services have been secured so that families with a first language other than English will not be excluded from participating in the research.

Families will be ineligible for the study if any of the following conditions apply: (1) there is active abuse or domestic violence within the family; (2) there is unmanaged mental illness within the family; (3) substance abuse is an issue within the family; (4) the family is living in an environment unsafe for the volunteer to visit; and (5) the family is under child protection orders or there are unsettled parenting arrangements. Families referred for volunteer home visiting will be assessed for eligibility by the local Volunteer Family Connect program coordinator according to the usual practice, and referrals will be made to other services within the community if the family is ineligible.

All current volunteers within the Volunteer Family Connect program will be invited to participate in the study. It is not possible to examine outcomes for volunteers employing a randomized controlled trial (RCT) design because this would halve the number of volunteers available and significantly impact program implementation. Instead, a community comparison sample will be recruited that will be matched on age, gender, education and employment levels, and geographical location.

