#### Recruitment

Family participants will largely be identified through the Volunteer Family Connect usual service referral networks, which include child and family health nurses, general practitioners, or family support workers. The Volunteer Family Connect program is advertised within the community, and parents are welcome to self-refer to the program. If eligible for the program, families will be invited to speak to a member of the research team and, if interested, informed consent for the research will be secured. The family will then be randomly allocated by the research manager using computer-generated random numbers to receive either the volunteer home visiting program in addition to usual care services (Intervention group = Volunteer Family Connect + usual care services) or the usual care services only (Control group = usual care services).

The procedure used to recruit and allocate families is summarized in Figure 2.

An invitation will be extended to all volunteers currently involved with the 7 participating sites to participate in the research. The matched community comparison sample will be recruited via one of the following two strategies: (1) volunteers will be asked to pass on an invitation to participate in the research to nonvolunteering acquaintances in their local networks and (2) the research will be advertised through Facebook, targeting the local areas in which the Volunteer Family Connect program is being trialed.

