Program Coordinators: Each site has an employed program coordinator with tertiary qualifications in social work or a related field. The program coordinators are responsible for recruiting and training the volunteers, establishing referral networks, matching volunteers with families, providing regular supervision to volunteers, conducting intake and progress interviews with families, and referring families to other services within the community.Trained volunteers: All community volunteers participate in a minimum of 30 hours of training before being matched with a family and must participate in two additional capacity-building sessions each year. Examples of core training modules include “a strengths-based approach to working with families,” “reflection on personal values and attitudes,” “boundaries and self-care,” “child development,” and “community resources.” The topics for ongoing capacity-building sessions are decided by the program coordinator depending on family needs at the time. For example, if there are high numbers of families who have infants, topics like “breastfeeding” or “sleeping and settling” may be chosen. All volunteers undergo a background check.Matching: Program coordinators match families with a volunteer, guided by the needs of the family but limited by the pool of volunteers available.Home visits: Volunteers visit the family for approximately 2 hours every week. What happens during visits will depend on the needs of the family. Volunteers are encouraged to support families to connect with other services and facilities within the community (eg, attend local playgroups, visit the child and family health center, go to the park, etc) and link them with information as needed. Volunteers are also expected to model positive interactions with the children and encourage the parents in their personal and family goals. Volunteers do not do cooking or housework tasks unless it is with the parent as part of helping them to learn how to do these tasks, and they do not provide child-minding or child care such as changing nappies or bathing children. Volunteers complete checklists following each home visit, detailing the activities and topics of discussion with the family and whether information was provided to the family or the family linked with another service in the community. The collated data are used as a measure of program fidelity and provide ongoing quality feedback to the service partner organizations.Exit interviews: The duration of the service will be a minimum of 3 months and a maximum of 12 months. When the family, volunteer, and program coordinator agree that the family has met their goals, the family is exited from the program and referred to other services by the program coordinator as appropriate.

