## Discussion

In this study, we aim to explore the effectiveness of a volunteer home visiting program designed to provide support to families with young children who might otherwise “fall between the cracks” because they are not eligible for intensive family support services but need more support than is available through universal primary services. The Volunteer Family Connect study will provide evidence of the outcomes for families based on the program logic of volunteer home visiting [1] and outcomes desired and valued by parents. This study assesses the effectiveness of volunteer home visiting on its own merits and contribution to the service landscape, rather than as a program equivalent to, or potential substitute for, professional services.

RCTs can be an uncomfortable methodological approach for not-for-profit organizations. Their employees are generally guided by an altruistic and empathic approach, rather than a rigidly scientific approach, and randomly denying support to someone they believe would benefit can be challenging. Time was spent with those delivering the program to discuss the ethical situation in the context of delivering the previously untested service that did not have evidence of effectiveness. The lengthy lead in time for this project was essential to secure support for the research across all levels of the organizations, from CEOs and board members, through to program coordinators and volunteers. Some volunteers and program coordinators did not want to be involved, and the services have also experienced some difficulties with their referral networks, with some referrers ceasing to refer families during the research trial. Understanding these significant challenges for participating organizations and their ongoing commitment to ensure a rigorous research approach is commendable. Launching this research is an indication that within the not-for-profit sector, rigorous research is feasible. It does, however, need to be embedded within trusting relationships and will need many formal and informal conversations across all levels of the organization, which can take several years.

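### When families outnumber volunteers, the allocation odds follow volunteer supply, which the coordinator who screens families knows and can influence, so allocation can be anticipated better than chance

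*Protocol article*

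**What the plan says.** The Allocation section of the protocol article describes individual computer-generated randomization for most families, "giving them an equal chance of being allocated to the intervention or the control group". It then makes an exception: "If more families are recruited than the number of available volunteers, randomization will be proportional using computer-generated randomizing". The example has five volunteers and seven families: "five of the seven families will be randomly allocated to the intervention group and two to the usual care group". The research program manager allocates without knowing anything about the family and tells the coordinator afterwards. The same section says that data collectors cannot be blinded and that families will know their arm.

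Three other sections bear on who knows the odds:

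- **Eligibility Criteria.** Referred families are "assessed for eligibility by the local Volunteer Family Connect program coordinator".
- **Delivery in the Trial.** "The program coordinators are responsible for recruiting and training the volunteers, establishing referral networks, matching volunteers with families". Also: "Program coordinators match families with a volunteer, guided by the needs of the family but limited by the pool of volunteers available".
- **Recruitment.** A member of the research team speaks to the eligible family, and then "informed consent for the research will be secured. The family will then be randomly allocated by the research manager".

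The Discussion reports the attitude of staff in the partner organizations: "randomly denying support to someone they believe would benefit can be challenging".

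**The concern.** Concealment is meant to stop whoever governs entry from foreseeing the arm a family will get. The stated safeguard protects a different step. It stops the manager from choosing by family, but it does not hide the odds from the coordinator. Under the exception, those odds depend on two local counts: families recruited and volunteers available. The coordinator screens the families and builds referral networks, and also recruits, trains and matches the volunteers. One person therefore sees both counts and has some influence on each.

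A coordinator who thinks a family particularly needs the service could put it forward when volunteers are plentiful relative to families, and put others forward when they are scarce. If the favoured families differ in prognosis, the arms differ at entry in an unadjusted comparison. Outcomes here are reported by parents who know their arm, and blind analysis does not correct selection at entry. The recorded discomfort with random denial of support makes the risk more than theoretical.

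**Working it through.** **1. The plan's own figure.** Let v be available volunteers and f recruited families. When f > v, P(intervention) = v/f; otherwise it is 0.5. With v = 5 and f = 7, 5/7 = 0.714, which matches the example of five to intervention and two to usual care.

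**2. How well allocation can be anticipated.** Someone who knows v and f guesses correctly with probability max(p, 1 − p).

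| v | f | P(intervention) | Best guess |
|---|---|---|---|
| 6 | 7 | 0.857 | 0.857 |
| 5 | 6 | 0.833 | 0.833 |
| 5 | 7 | 0.714 | 0.714 |
| 4 | 7 | 0.571 | 0.571 |
| 1 | 3 | 0.333 | 0.667 |
| 1 | 2 | 0.500 | 0.500 |

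Under 1:1 the guess rate is 0.50. If the results of a 5:2 batch were released one at a time (an assumption, since the article does not say), simulation of 200,000 batches gives a guess rate of about 77%, with about 29% of assignments already determined when they are made.

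**3. No free volunteer.** For a family handled alone (f = 1), f > v only when v = 0. With v of 1 or more the family stays at 50%. With v = 0 the formula gives 0/1 = 0. The article does not address this case.

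**4. Size of the possible bias.** Assume that a fraction q of families is steered to p = 5/6, that the rest enter at 1/2, and that the two groups differ by g SD in prognosis. Then:

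- share steered in the intervention arm: A = (5/6)q / [(5/6)q + (1/2)(1 − q)]
- share steered in the control arm: B = (1/6)q / [(1/6)q + (1/2)(1 − q)]
- unadjusted bias: (A − B)g

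For q = 0.10: A = 0.0833/0.5333 = 0.156 and B = 0.0167/0.4667 = 0.036, a difference of 0.121. At g = 0.2 the bias is 0.024 SD; at g = 0.5 it is 0.060 SD.

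For q = 0.20: A = 0.1667/0.5667 = 0.294 and B = 0.0333/0.4333 = 0.077, a difference of 0.217. At g = 0.2 the bias is 0.043 SD; at g = 0.5 it is 0.109 SD.

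The range is about 0.02 to 0.11 SD. The values of q, g and the 5/6 odds are assumptions, not figures from the article. The Quantitative Analysis section treats an effect size of about 0.5 as clinically meaningful, so the range is roughly 0.02/0.5 = 4% to 0.11/0.5 = 22% of that.

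**5. Is the exception needed in its own example?** At 1:1, seven families need only three or four volunteers, and five are available.

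**The case against.** The strongest reply is that the coordinator learns a probability and not an assignment. Most families enter at 50%. Within a batch every family has the same chance, so the coordinator cannot pick which one gets the volunteer. The research team takes consent between screening and allocation, the manager draws by computer, and the coordinator hears the result afterwards. The article does not say who reports the volunteer count or decides when a batch is drawn. It mentions staff discomfort to explain the long lead-in, and reports no manipulation of entry. All of this stands. It limits the size of the problem, but leaves the screener knowing when the odds are above or below one half.

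A reader might go further and infer that the coordinator controls the count, that the next assignment is predictable, or that families entered with no free volunteer are controls who were never randomized. The documents do not support these readings. Certain control at zero volunteers follows from extending v/f to a case the article never addresses; holding the family until a volunteer is free fits the text equally well, and the full protocol may settle it. Any figure for the share of controls never randomized would rest on that unstated practice.

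Supposing half of all families were steered would also contradict the statement that most have an equal chance. It would give an intervention share of (5/6 + 1/2)/2 = 2/3, or 200:100, against the planned 150:150.

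Finally, if a batch is drawn at once, assignment within it is random, so stratifying by batch or ratio would remove the bias in step 4. That figure applies to unadjusted comparisons, such as the t tests the article names.

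**Conclusion.** The concern holds in a limited form. Tying the odds to volunteer supply weakens concealment whenever families outnumber volunteers, because the person who screens families knows that supply and can influence it. The best guess rises from 50% to 71% in the article's own example. The effect on an unadjusted comparison is modest under plausible steering, about 0.02 to 0.11 SD, and its direction is unknown because the favoured families could have the better or the worse prognosis. That range depends wholly on the assumed 10% to 20% steered, 5/6 odds and 0.2 to 0.5 SD gap; the article gives no data on how often the exception applied.

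The zero-volunteer case is unspecified. Read literally, the rule would send such a family to control with certainty, but the article does not say that this happens. The point deserves correction because the remedy is cheap and fits the stated equal chance and 150:150 target.

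**What to change.** **Allocation rule.** Replace the supply-driven ratio with a 1:1 sequence per site, held centrally by the research manager, with random block sizes unknown to coordinators. Release one assignment per family after eligibility and consent are locked. State that a family is not randomized while no volunteer is free at the site, and fix entry order by consent date so that families cannot be re-ordered. Volunteer supply would still affect when a family is randomized, but no longer its odds.

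**Families already entered.** Record the volunteer count and the ratio in force at each allocation. Keep all randomized families in the intention-to-treat analysis, stratified by batch or ratio. Report a sensitivity analysis without any family whose probability of intervention was zero, if there were any.

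**Cost.** An amendment to the allocation paragraph, a pre-generated list in the existing computer system and a look back through the allocation records. No extra staff or families are needed. The downside is a short wait for some families and slightly slower use of volunteers.

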#### Sample Size

We aim to recruit 300 families to the study, 150 to the intervention group (Volunteer Family Connect + usual services) and 150 families to the control group (usual services). Recruitment of 150 families per group has been undertaken based on what is feasible given current caseloads in the participating sites and also so that, allowing for attrition, data analysis can be conducted with a final sample size of 100 families per group. A sample size of 100 families per group has power of .80 at the 95% level to detect effect sizes (ESs) of .5 or larger for the PSCS Satisfaction subscale (significant differences detected with minimum n=16 per group) and the Client Enablement Index (significant differences detected with minimum n=7 per group) based on pilot study findings and a previous trial of nurse home visiting conducted by one of the chief investigators on this study [34].

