### Data Analysis

#### Quantitative Analysis

Primary and secondary outcomes will be extracted and analyses conducted using SPSS Version 25.0. Analysis will be completed both on an intention-to-treat and a per-protocol basis. Families will be considered to have received the scheduled dose if they receive visits from the volunteer for at least 3 months with no gap between visits of more than 2 weeks. Volunteer outcomes will be analyzed using cross-sectional comparative analysis. Participant demographic data will be analyzed using basic descriptive statistics. Prior to the analysis of outcome measures, data will be assessed for outliers and normality. Scale variables will be analyzed using independent *t* test or analysis of variance or their nonparametric counterparts (eg, Mann–Whitney U test) if appropriate. Mixed modeling will be completed on the primary and secondary family outcomes to assess the effect of the intervention over time while adjusting for possible confounders. Categorical variables will be analyzed using odd ratios or chi-square analysis. For all analyses, two-tailed tests will be undertaken: findings with α<0.05 will be determined to be statistically significant. ESs will be calculated for all trends (α<0.1) and statistically significant findings; (ES≈0.5 [Cohen *d*]) will be considered clinically meaningful. Overall, the program will be considered to have been effective if at least one of the primary outcomes is positive and the other is neutral.

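### The chance of intervention varies with local volunteer supply, and the listed two-group tests ignore this, so they are biased if outcomes differ where the ratios differ

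*Protocol article*

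**What the plan says.** All references are to the protocol article.

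- **Allocation, default.** Individual computer randomisation is the rule for the majority of families, and it is described as "giving them an equal chance of being allocated to the intervention or the control group".
- **Allocation, exception.** "If more families are recruited than the number of available volunteers, randomization will be proportional using computer-generated randomizing". The worked example is that "if there are five available volunteers and seven recruited families, five of the seven families will be randomly allocated to the intervention group", with the other two going to usual care.
- **Sample Size.** "We aim to recruit 300 families to the study, 150 to the intervention group", with an equal number of controls. No allowance is made for the exception.
- **Quantitative Analysis.** Scale outcomes are compared by an independent t test, "analysis of variance or their nonparametric counterparts", and categorical outcomes by odds ratios or chi-square. None of these carries a term for site, batch or allocation ratio. Mixed modelling of the primary and secondary family outcomes, with adjustment for potential confounders, is also planned. Its covariates are not named, and the section does not say whether the two-group tests or the mixed model settle the primary question.

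**The concern.** Two features combine.

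First, the trigger does not match its purpose. Under 1:1 only about half the families need a volunteer, so supply runs short only when families exceed about twice the volunteers. The rule starts as soon as families exceed volunteers. Tightening supply therefore first raises the chance of intervention sharply, and lowers it below one half only much later.

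Second, the ratio depends on local supply and demand at the time, so it can differ by site and by period. The article gives reasons to expect such variation. Its seven sites span city, suburban and rural settings in four states (Development), and the Discussion reports that some referrers stopped referring during the trial and that some volunteers and coordinators did not want to take part. If families in the sites or periods with a 5:2 ratio have better or worse outcomes for reasons unrelated to the program, they are over-represented in the intervention arm, and a pooled comparison counts part of that difference as treatment effect. The bias can go in either direction.

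The program is to be called effective if one primary outcome is positive and the other neutral, so a false positive on a single outcome could decide the trial.

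**Working it through.** **The plan's own power figure.** Sample Size states: "A sample size of 100 families per group has power of .80 at the 95% level to detect effect sizes (ESs) of .5 or larger". With a two-sided 5% level, power = Φ(d/√(1/n₁+1/n₀) − 1.96) = Φ(0.5/√(2/100) − 1.96) = Φ(1.58) = 94% (94.0% with the t distribution). The stated .80 does not reproduce; 80% needs 63 to 64 per group. The stated figure is conservative, and this point does not depend on it.

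**The trigger.** With five volunteers, the chance of intervention is 0.50 up to five families and 5/F for F families beyond that.

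| Families | Chance of intervention | Volunteers needed at 1:1 |
|---|---|---|
| 5 | 0.50 | 2.5 |
| 6 | 0.83 | 3.0 |
| 7 | 0.71 | 3.5 |
| 8 | 0.63 | 4.0 |
| 9 | 0.56 | 4.5 |
| 10 | 0.50 | 5.0 |
| 11 | 0.45 | 5.5 |

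From six to nine families the rule moves away from 1:1 although five volunteers would cover it. A real shortage begins at eleven.

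**Bias of a pooled comparison.** Let a share f of families be allocated 5:2 and the rest 1:1, and let mean outcome differ by D (in SD units) between the two sets, with no treatment effect.

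- Share of the intervention arm from 5:2: s₁ = (f·5/7) / (f·5/7 + (1−f)/2)
- Share of the control arm from 5:2: s₀ = (f·2/7) / (f·2/7 + (1−f)/2)
- Bias = (s₁ − s₀)·D

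The article gives neither f nor D. Because it says that most families are 1:1, f is taken as 10% to 30%. D is taken as 0.3 or 0.5 SD. For f = 0.3: s₁ = 0.2143/0.5643 = 0.380, s₀ = 0.0857/0.4357 = 0.197, difference 0.183.

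| f | s₁ | s₀ | Bias, D = 0.3 | Bias, D = 0.5 | Expected split of 300 | Power at d = 0.5, one third lost |
|---|---|---|---|---|---|---|
| 10% | 0.137 | 0.060 | 0.02 SD | 0.04 SD | 156:144 | 94.2% |
| 20% | 0.263 | 0.125 | 0.04 SD | 0.07 SD | 163:137 | 94.1% |
| 30% | 0.380 | 0.197 | 0.05 SD | 0.09 SD | 169:131 | 93.9% |

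The one-third loss is the article's own 150 to 100 per group. Against the effect of about 0.5 that the article calls clinically meaningful, 0.04 to 0.09 SD is 8% to 18%.

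**Type I error.** Simulation with 200 analysed families, normal outcomes, no treatment effect and 4,000 runs per cell (simulation standard error near 5% is √(0.05·0.95/4000) = 0.3 points):

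| f | D | Pooled t test | Model with a term for the ratio in force |
|---|---|---|---|
| 20% | 0.3 | 6.2% | 5.1% |
| 20% | 0.5 | 7.4% | 4.8% |
| 30% | 0.3 | 6.1% | 4.8% |
| 30% | 0.5 | 9.6% | 5.0% |

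With the ratio in the model the mean bias is 0.00 in all four cells.

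**The case against.** The strongest reply is that the article also plans a mixed model with confounder adjustment on these same outcomes. That model could remove the bias, and a condensed article may leave its covariate list to a statistical analysis plan that is not shown. This stands in part: the article does not commit the trial to an unadjusted answer. But it does state the pooled tests, and it does not say that the model outranks them. The ratio in force is a known feature of the design, so conditioning on it should not depend on whether it is later picked as a confounder.

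It is also fair that the bias is conditional. It needs both a mix of ratios and outcome levels that track them; if every family were 5:2 there would be none. The article gives no size for outcome differences between sites. Its secondary question on location concerns variation in outcomes among intervention families, which is suggestive only.

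A reader might infer three stronger points that the documents do not support:

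- **Power is damaged.** It stays near 94% at a 30% share, and is 89% even if all families were 5:2 (143:57 analysed), above the stated .80.
- **The 150:150 split is lost.** It is an aim, most families stay 1:1, and beyond two families per volunteer the rule favours control. Departure is possible, not certain.
- **Coordinators can foresee or steer allocation.** They know the volunteer pool, but nothing says that they see the odds. Consent precedes allocation, and the manager who allocates knows no family details.

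**Conclusion.** The point holds in a conditional form. The rule makes the chance of intervention depend on local volunteer supply, and departs from 1:1 where 1:1 is still feasible. The two-group tests, followed as written, ignore this and are biased if outcomes differ between the sites or periods in which the ratios differ. On the assumptions shown (10% to 30% of families at 5:2, outcome differences of 0.3 to 0.5 SD), the bias is about 0.02 to 0.09 SD. At a 20% to 30% share, type I error is roughly 6% to 10% in place of 5%. That is modest, but enough to turn a borderline primary result. The documents do not show that the bias has occurred. The harm at issue is validity of the comparison, not sample size.

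**What to change.** **Main change, to the analysis.** Record for each family the site, the randomisation batch and the allocation ratio in force. Stratify or adjust every between-arm comparison for them:

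- Name them as terms in the mixed model, and state that this adjusted analysis decides the primary question.
- Replace the pooled tests by stratified or adjusted versions, or label them descriptive.
- Where ratios such as 5/6, 5/7 and 5/8 across seven sites leave sparse strata, use site plus the allocation probability, or inverse-probability weights.

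**Secondary change, to allocation, only for families still to be randomised.** Keep 1:1 while volunteers cover half the waiting families, and use proportional allocation only beyond that. This does not replace the analysis change, because the ratio can still vary. It may also reach few families: data collection is to end by the close of 2018 and follow-up lasts 15 months, so a family needs to enter by about September 2017 for full follow-up.

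**Cost.** A few degrees of freedom, and some work to retrieve the ratio from the randomisation records, which the article does not say are kept in that form. The terms should be fixed before any analysis by arm.
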